## Abstract

**Background:**

One of the most important risk factors for childhood depression is being the child of a depressed parent. These at-risk children have two to four times the probability of having an affective episode compared with their peers. Preventive interventions such as Beardslee’s Preventive Intervention Program (PIP) that are targeted at children of depressed parents have proven effective in many countries. The PIP is a family-based approach that works by promoting resilience in children and increasing positive interactions within the family. In this pilot randomised controlled trial (RCT), we will determine the acceptability and feasibility of an adapted version of this intervention in Chile.

**Methods/design:**

We are conducting a pilot RCT with a manualized intervention. The intervention will be delivered in seven weekly sessions at the family home. It is targeted mostly at parents but will also measure outcomes among the children. Control subjects will follow their treatment as usual. Feasibility and acceptability will be assessed by recruitment, adherence, dropout and level of missing data, as well as the burden of scales and measurement tools. Families will be followed for 11 months.

**Discussion:**

Given the negative lifelong consequences of depression and the burden they represent, preventive programmes are not only feasible but necessary. Despite the successful implementation of this intervention in different countries, an adaptation to the Chilean reality will be prerequisite. The results of this pilot study will inform a definitive trial that will make the case for its national implementation.

**Trial registration:**

Clinicaltrials.gov trial identifier: NCT02593266. Registration date: 30 Octo 2015.

## Background

Major depression is a prevalent and disabling condition that constitutes an important public health problem in Chile. This growing problem has been identified by numerous organizations as a major health-care priority in the country [1].

In the Chilean population, depressive disorders represent the second leading cause of specific disease [2]. Its prevalence, according to the latest national health survey, is 17.2 %, and is higher in women with fewer than 8 years of education [3]. More than 30 % of women consulting in primary health care have a diagnosis of depression. It is the second leading cause of disability in Chilean women, as measured by disability-adjusted life-years, and the fourth leading contributor to the global burden of disease [4, 5]. This disorder leads to greater disability than other chronic diseases, such as hypertension and diabetes, and explains over 40 % of sick leaves [1].

Depression is not a problem that affects only adults. In fact, 8 % of adolescents in Chile have major depression at any given time, and the lifetime prevalence of depression is 14 % [6]. Using the Beck Depression Inventory-II (BDI-II), researchers in a study in the city of Concepción found that 32.6 % of 746 secondary school students had depressive syndrome [7].

One of the most important risk factors for childhood depression is being the child of a depressed parent [6]. In fact, by age 20, a child with an affectively ill parent has a 40 % chance of having an episode of depression, and by age 25, this rate increases to 60 % [8]. These rates are two to four times higher than rates among their counterparts from homes without parental illness [9, 10]. Having a parent with depression is also associated with an increased risk of anxiety disorders and a variety of other problems, including poor health and deficits in academic performance, social relationships and self-esteem [10, 11].

One possible environmental mechanism for the transmission of depression from parent to child is the quality of the parenting that the child receives [12, 13]. Parental depression negatively affects caregiving, material support and nurturance. Observational studies have documented numerous parenting difficulties among depressed mothers, including increased hostility, higher rates of negative interactions and impatient use of directives in guiding their children’s behaviour [13–15]. In other studies, depressed mothers have been found to be less responsive to their children’s behaviour, to communicate less effectively, to demonstrate lower synchrony with their infants, and to have fewer positive interactions with their children [16, 17]. In turn, quality of parenting has been found to be related to depression in children and adolescents (see [18] for a meta-analysis).

All of this, coupled with the fact that there is a big gap between the population of adolescents in Chile who manifest some form of mental health disorder and the population of adolescents who ultimately receive treatment, creates a very large need for preventive strategies.

*Prevention* refers to interventions before the onset of a disorder that are designed to prevent the disorder’s occurrence [19]. Preventive strategies are aimed at reducing the incidence, prevalence and recurrence of mental disorders; the time spent with symptoms; the risks for such mental illnesses; and the effects of illness on affected people, their families and society [20]. Recent efforts to develop preventive interventions for depression have been successful and suggest that depression is amenable to a public health approach to disease prevention [21, 22]. A preventive approach to mental illness is not only desirable but feasible and, according to a recent meta-analysis, also cost-effective [23].

To date, mental health interventions for depression have been focused almost exclusively on an individual treatment approach, but selective preventive interventions that are targeted at community individuals or groups demonstrating a higher than average risk have a strong evidence base [24]. A recent meta-analysis by Siegenthaler and colleagues of randomised controlled prevention trials showed that, in children of parents with a mental disorder, the risk to offspring for the same mental disorder was reduced by 40 % [25].

There are a number of selective prevention strategies designed specifically for children of parents with depression that have been successful, and that have in common a focus on strengthening parenting and addressing youth needs. Beardslee and colleagues reviewed important national programmes such as those of Finland and Australia [26].

In Finland, the Effective Child and Family Programme is supported by the Ministry of Social Affairs and Health, which intends to make a system change in health and social services so that professionals can attend to the needs of adult patients and their children. The programme incorporates families with psychiatric problems to promote children’s well-being and to prevent children’s problems. Some of the strengths of the programme are its multilevel structure and the application of family intervention sessions similar to those of the Beardslee Preventive Intervention Program (PIP) for Depression [26].

Australia has developed the Children of Parents with a Mental Illness national initiative to support families with a parent with depression. Here, a version of the PIP for Depression was used with the Family Talk technique. Systematic approaches, such as those used in Finland and Australia, offer the best opportunity for large-scale impact, and there are important strategies that practitioners can employ directly with families [26].

### The Beardslee Preventive Intervention Program for Depression

Beardslee’s PIP is one of few methods in the field that uses family-based methods developed for preventive practice among children of parents with depressive disorders and mental illness [27]. It has been implemented in Sweden and Finland on a national level, and it also has been successful in the Netherlands, Norway, Sweden, Colombia, Costa Rica, Iceland, and Chicago in the United States [28].

The main purpose of the PIP is to prevent depression and other mental health problems in children of depressed parents by promoting resilience of children and increasing positive interactions within the family. Resilience is the reason why many children of depressed parents do not develop symptomatology; it enables them to accomplish age-appropriate developmental tasks, engage in relationships and understand their surroundings despite their parents’ illness [29, 30]. This programme generates opportunities for resilience promotion in children by supporting families to identify and build upon these resilience processes. Resilience is an important protective factor that can counterbalance the multiple risk factors for depression among children and adolescents, such as by developing the ability to understand their parents’ illness and move on [31]. On the other hand, the parents’ resilience that this programme builds upon is the capacity to remain committed to parenting despite depression and to reflect on how they could become effective parents [32].

The PIP’s aim is to provide psychoeducational material, to link that to the family’s life experiences; to increase understanding within the family; and, in that way, to help them find their own strengths, begin to plan to overcome depression and be able to have family conversations about depression. Negative interactions are one of the proximal mechanisms through which the effects of parental depression are transmitted to children [33]. Including conversation skills in this intervention, improving communication about parental illness in the family, promoting other protective factors for the children, and strengthening the parents in their role as caregivers are strategies also used for enhancing resilience [34]. Communication and openness about the parent’s illness within the family improves children’s understanding of parental illness and their own situation—also a characteristic of resilient adolescents [30]—and enhances parental and family functioning. Parents are also provided with information about the other well-known protective factors for the children, such as school, friends and interests, and are encouraged to support these.

The PIP is a manualised method available in Spanish that has been offered in two public health formats: two lectures for parents and a seven-session intervention called Family Talk. In the latter version, both parents are given an opportunity to talk about their experiences and the impact of the illness on themselves and their children. Parents’ concerns about their children are paid attention to, as are their questions about the children. Each child is then interviewed individually with a focus on the child’s experiences of the parent’s illness. Protective risk factors for the child are assessed. Subsequently, parents are given feedback from the child’s interview, and a family session is planned with the children’s questions and experiences as a basis. In the family session, parents are encouraged to talk about their illness with the children by themselves in order to start a process towards mutual understanding within the family. Follow-up after 1 and 6 months is recommended, with the aim of checking on the family, addressing concerns and reviewing protective factors for the children.

Beardslee’s family intervention has evidence of long-term effects for children and their families [35–37]. Outcomes included diminished adolescent internalizing symptoms, increased positive family interactions, and increased rates of recognition and treatment for children who did eventually experience depression [38].

Given the prevalence and burden of depression in Chile, a preventive intervention such as the PIP for Depression is much needed. This intervention needs to be adapted and integrated into the Chilean reality first.

### Aims and objectives

The aim of this study is to evaluate the acceptability of an adaptation of Beardslee’s PIP for Depression in Chilean families. Additionally, we will test the feasibility of implementing this programme broadly. The main objectives therefore are as follows:To determine whether the PIP for Depression is acceptable for Chilean familiesTo assess recruitment processes and study uptake to inform the feasibility of a full-scale randomised controlled trial (RCT)To evaluate the burden of scales and measurement toolsTo measure response, dropout rates and level of missing data

The effects of the family intervention on parental depression will be evaluated. Internalising and depressive symptoms in children and their global psychosocial functioning will also be measured.

## Methods/design

### Setting

The first evaluation will happen at the families’ nearest mental health centre; subsequently, the intervention will be carried out in people’s homes. Families will all be living in Recoleta, a 16-km^2^ urban subdivision of Chile’s capital city of Santiago comprising 148,220 habitants. Within this catchment area, participants will be contacted via the five mental health centres available.

### Design

The present study is a pilot trial and will therefore be primarily exploratory. It will provide qualitative information in terms of how feasible and accepted the PIP for Depression could be for Chilean families. The design of the quantitative side of the study will be a single-blind RCT. The intervention group will receive PIP for Depression at their home in addition to their usual treatment for depression, whereas participants in the control group will be on a waiting list for the intervention and will receive their treatment as usual (pharmacotherapy and/or psychotherapy).

### Primary outcomes

Acceptability will be assessed by determining how well the intervention is received by the target population and the extent to which this new intervention might meet the needs of the target population. Feasibility will be ascertained by looking at whether the aims of the study are achieved and appraising whether, judging by the general experience in the pilot study, an upscaled project is likely to succeed. The recruitment and intervention processes will be scrutinised.

### Secondary outcomes

The following are secondary outcomes to be considered:Depressive symptoms in both the child (Children’s Depression Inventory) [39] and the parent (BDI-II) [40]Family function (Family Adaptability and Cohesion Evaluation Scales [FACES]) [41]Parental competence (Positive Parenting Scale-Second Edition [E2P]) [42]Adaptive behaviour in the child (Child Behaviour Checklist [CBCL]) [43]Resilience in the child (School Resilience Scale [ERE]) [44]Cognitive function (Wechsler Intelligence Scale for Children-Third Edition [WISC-III] Processing Speed Index, which includes coding and symbol search subtests) [45]

The hypotheses for the intervention are as follows:Children in the intervention group will not show an increase in depressive and internalising symptoms as compared with those in the waiting-list control group.Parents in the intervention group will have increased their family functioning scores and decreased their general psychopathology scores compared with those in the control group.

### Materials

#### Sociodemographic questionnaire

A brief questionnaire was designed to collect sociodemographic information on the parents and their children. Questions on age, gender, education level, occupation and work status of every person living in the household were included. Information on household income in the last year and the last month was also obtained.

#### Qualitative measures

Acceptability will be measured via qualitative feedback forms after each session. These forms will include questions on the participants’ thoughts and opinions about the intervention content and its delivery. They will include items such as, “How relevant to you and your family’s issues was this module?”, “How satisfied were you with today’s session?”, and “In your opinion, is there anything that prevented the session from suitably taking place?” The feedback obtained from this questionnaire will be used to continuously optimise the intervention. Furthermore, at the end of the intervention, focus groups will be created for families and therapists. Forms designed to determine which components of the intervention are covered in each session will be completed to ascertain the integrity of the intervention and adherence to the manual. To further examine the acceptability of the intervention and adherence to the manual, 20 % of the total number of sessions in the studies will be videotaped for those families who give their consent.

The feasibility of this pilot study requires that the intervention be effectively carried out with an adequate number of families and within the delineated time. The feasibility of the recruitment process will include the number of families sampled and contacted, those families who accept, the number of families who complete the intervention and reasons for ineligibility, and non-participation or early withdrawal from intervention. The feasibility of the intervention will include the number of sessions attended, time taken to complete questionnaires (burden of questionnaire completion), items left blank on questionnaires, follow-up rates and dropout. The number of therapists available and how many families they manage to visit per week will also be noted. As it is important to evaluate whether the administration and assignation of resources is effective, supervisors at health centres will also be interviewed.

#### Quantitative measures

The following quantitative measures will be used:M.I.N.I.: The Mini International Neuropsychiatric Interview (M.I.N.I.) version 5.0 [46] is a brief structured diagnostic interview developed in 1990 by doctors and psychiatrists in the United States and Europe. With a delivery time of approximately 15 minutes, the M.I.N.I. 5.0 is a diagnostic tool for psychiatric disorders based on the *Diagnostic and Statistical Manual of Mental Disorders, Fourth Edition* (DSM-IV), and the International Classification of Diseases, Tenth Revision.BDI-II: The BDI-II is a self-assessed multiple-choice scale consisting of 21 questions. It is one of the most widely used instruments in the world that measures the severity of depression. It is designed for people older than 13 years of age and consists of items that measure depressive symptoms, hopelessness, irritability, guilt and physical symptoms.E2P: The Positive Parenting Scale (E2P) is a self-administered 54-item questionnaire on parental skills which covers four subcategories: bond, development, protection and self-reflection.FACES-II: This is the second version of FACES, a self-administered scale measuring cohesion and adaptability in the family. There are 50 items, 25 of which are intended to explore the dimension of cohesion and the remaining 25 adaptability.MINI-Kid [47]: The Mini International Neuropsychiatric Interview for Children and Adolescents (MINI-Kid) is the children’s version of the M.I.N.I. The structure is identical, but the questions are modified to facilitate the understanding of children.CDI: The Children’s Depression Inventory assesses depressive symptoms and provides a total score for depression in children. It may be self-administered by the children, but in this investigation it will be administered by an evaluator. It consists of 27 items, each consisting of 3 statements, and measures 2 dimensions: dysphoria (depressed mood, sadness, worry, and so forth) and negative self-esteem (judgments of inefficiency, ugliness, evil, and so forth).CBCL: The Child Behaviour Checklist scale is completed by parents to detect emotional and behaviour problems in children and adolescents. It consists of 113 questions, scored on a 3-point Likert scale (0 = absent, 1 = happens sometimes, 2 = often occurs). This scale provides information on the following syndromes: anxiety, depression, somatic complaints, social problems, thought problems, attention problems, and rebellious and aggressive behaviour. Also, it has six scales based on DSM-IV diagnostic categories: emotional problems, anxiety, somatic problems, attention-deficit/hyperactivity disorder, oppositional defiant problems and behaviour problems.School Resilience Scale (ERE): This scale contains 27 items for children between the ages of 9 and 14 years. The ERE measures the level of overall resilience of children and pre-adolescents in three main areas (I am, I can and I have) subdivided into five dimensions: self-identity, network models, learning generativity, internal resources and external resources.WISC-III: Two subscales of the WISC-III will be administered to measure processing speed. In the coding test, there is a series of simple forms (coding A) or numbers (coding B), each of which has a corresponding code, and the child is asked to draw the symbol under its corresponding form or number according to a key. In the symbol search test, the child is asked to decide whether target symbols appear in a row of symbols.

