#### Inclusion criteria for families

Patients will be eligible if they are currently undergoing a depressive episode or if they have done so in the past 3 months. Eligible patients must have at least one non-depressed child between the ages of 6 and 12 years. In families in which only one parent has a depressive disorder, this parent will be the “identified parent” (IP) and the parent who does not have a disorder will be the “unidentified parent”. If both parents have depression, the parent with the most severe or chronic mood disorder will be designated as the IP.

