#### Exclusion criteria

The following are the exclusion criteria for parents:Alcohol or drug dependence or abuse as assessed with the M.I.N.I., or being in treatment for substance usePsychosis, personality disorder, bipolar disorder or suicide ideation as assessed with the M.I.N.I.Having a relationship crisis with a current partner, assessed by self-report or by having attended couple’s therapy in the past monthAttending family therapy

The following are the exclusion criteria for children:Being outside the age range of 6–12 years at the time of recruitmentInability to understand or answer age-appropriate questionnaires (due to intellectual disability or otherwise)Having depression as assessed with the M.I.N.I.-KidBeing in treatment for or having taken psychotropic medication in the last month

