#### Sample size calculation

Despite the fact that a power calculation is not fully appropriate for a feasibility study [48], we have estimated a suitable number of children for this study. We expect that the proportion of children who will develop depressive symptoms within 1 year in the waiting-list control group will be 0.33, compared with 0.05 for those children in the intervention arm. For a loss to follow-up calculated at 15 % and in a two-sided contrast analysis, 32 children will be required per arm and 64 children in total. Despite there being evidence to support a one-sided analysis for this case, since we assume the intervention will not cause harm, we will carry out a two-sided analysis as is common in RCTs. This number is adequate according to recommendations for feasibility studies which propose a minimum of 30 participants per arm to estimate parameters for future sample size calculations [49, 50].

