#### Follow-up

All families will be assessed at the same time points after being included in the study. For families in the intervention group, this translates into the following five phases: pre-intervention, post-intervention, 3 months post-intervention, 6 months post-intervention and 9 months post-intervention. Since the intervention should last around 2 months, follow-up points for families in the control group would translate into the following five stages: baseline and 2 months, 5 months, 8 months and 11 months after baseline.

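### The resilience scale (ERE) is described as for ages 9 to 14 but is listed without an age limit as an outcome in children enrolled at 6 to 12, and no validity below age 9 is shown

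*Protocol article*

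**What the plan says.** Under Quantitative measures, the article describes the ERE: "This scale contains 27 items for children between the ages of 9 and 14 years". Under Secondary outcomes it lists "Resilience in the child (School Resilience Scale [ERE", with no restriction by age.

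The children enrolled are younger than that range allows. Inclusion criteria for families reads "Eligible patients must have at least one non-depressed child between the ages of 6 and 12 years", and Exclusion criteria removes only children "outside the age range of 6–12 years at the time of" recruitment. Assessments are at "baseline and 2 months, 5 months, 8 months and 11 months after baseline" (Follow-up).

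The feasibility measures, under Qualitative measures, include the time taken to complete questionnaires and "items left blank on questionnaires". Evaluating the burden of the scales and the level of missing data are both listed among the main objectives.

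**The concern.** The two age ranges stand in the same document and overlap only at 9 to 12. Followed as written, the plan yields ERE scores from 6-, 7- and 8-year-olds for whom the article offers no younger version, no adaptation and no evidence of validity.

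Three things are at stake:

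- **Interpretation of the resilience result.** The article presents the promotion of resilience as one of the main ways the programme is meant to work, and the ERE is the only child resilience measure listed. A mean that pools in-range and off-range scores is hard to interpret, and so is any variance estimate carried forward to the full trial.
- **Interpretation of burden.** If young children leave ERE items blank or take long over them, a pooled figure cannot separate ordinary questionnaire burden from a mismatch between form and age.
- **Change over time.** Some children start below 9 and pass it during follow-up, so the same child can contribute both off-range and in-range scores.

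**Working it through.** **1. Inputs from the article.** ERE range 9 to 14 (Quantitative measures). Enrolled ages 6 to 12, judged at recruitment (inclusion and exclusion criteria). Assessments at 0, 2, 5, 8 and 11 months (Follow-up). 32 children per arm, 64 in total, with "loss to follow-up calculated at 15" per cent (Sample size calculation).

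**2. The plan's own sample size.** The expected proportions are "in the waiting-list control group will be 0.33, compared with 0.05 for those children in the intervention arm". Significance level and power are not stated; assume two-sided 0.05 and 80%. With unpooled variance:

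n = (1.960 + 0.842)² × (0.33×0.67 + 0.05×0.95) / 0.28² = 26.9, so 27 per arm; 27 / 0.85 = 31.8, so 32 per arm.

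This reproduces 32 and 64. (A pooled-variance formula gives 30, or 36 after loss.) The age point does not depend on this calculation; 64 is used only to size the affected group.

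**3. Age years out of range.** In completed years, 6 to 12 is seven years. Ages 6, 7 and 8 are below 9, so 3/7 = 42.9% of the enrolled age years are outside the range. This count is exact, but it is a share of age years, not of children.

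**4. Children out of range.** The age distribution is not given, so the share under 9 is an assumption. Number out = 64 × share, rounded; in range per arm = (64 − number out) / 2; after loss, × 0.85.

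| Share under 9 at baseline (assumed) | Out of range | In range | In range per arm | Per arm after 15% loss |
|---|---|---|---|---|
| 20% | 13 | 51 | 25.5 | 21.7 |
| 30% | 19 | 45 | 22.5 | 19.1 |
| 3/7 (even spread) | 27 | 37 | 18.5 | 15.7 |
| 50% | 32 | 32 | 16.0 | 13.6 |
| 60% | 38 | 26 | 13.0 | 11.1 |

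**5. Crossing age 9 during follow-up.** With an even spread (assumed), the share still under 9 after m months is (3 − m/12) / 7:

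| Month | Share under 9 | Of 64, before loss |
|---|---|---|
| 0 | 42.9% | 27.4 |
| 2 | 40.5% | 25.9 |
| 5 | 36.9% | 23.6 |
| 8 | 33.3% | 21.3 |
| 11 | 29.8% | 19.0 |

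About 27.4 − 19.0 = 8 children would cross by month 11, but only 27.4 − 25.9 = 1.5 by month 2. The planned two-way analysis of variance defines time as before versus after treatment, so crossing matters little there and more for the later assessments. At the upper end there is no problem: a child under 13 at recruitment is still under 14 at month 11.

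**6. Does other text resolve it?** No section limits the ERE to children of 9 or over, names a version for younger children, or argues for use below 9. The exclusion for children who cannot understand or answer questionnaires suited to their age does not remove 6- to 8-year-olds; it presupposes forms that fit the child's age. For the Children's Depression Inventory the article does state a change in administration (by an evaluator); for the ERE it states none.

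**The case against.** **The article never says that every child receives the ERE or that scores will be pooled.** True. Stating the range openly is compatible with use in the eligible subset, and which child receives which form is often left to a full protocol. But the outcome is listed for the child without qualification, and both ranges are printed and conflict. That is a contradiction in the text, not merely an omitted detail.

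**A reader might infer that 6- to 8-year-olds cannot be validly scored, or that floor and comprehension effects will follow.** The article does not support this. It gives a target age range but no norms, scoring rules or reading level. What stands is that validity below 9 is not shown.

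**A reader might infer that the feasibility results are contaminated.** This also goes too far. Learning how burdensome the forms are is an aim of the pilot, and difficulty with the ERE in young children is real burden of the battery as given. Of the item counts stated (21 + 54 + 50 + 27 + 113 + 27 = 292), the ERE contributes 27, about 9%, and tabulating blanks by instrument would expose a problem. What remains is that an ERE figure pooled over ages mixes two causes.

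**The outcome is minor.** It is one of several secondary outcomes in an exploratory pilot, neither stated hypothesis names resilience, and the sample size does not rest on it. This limits the weight of the point without removing it.

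**Withholding the form from younger children would discard pilot information.** Correct; the remedy therefore need not stop its administration.

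**Conclusion.** The mismatch is real and explicit: three of the seven enrolled age years lie below the ERE's stated range, and the article shows no validity there. That part needs no assumption.

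The number of children does. With 20% to 60% under 9, 13 to 38 of 64 are out of range, leaving about 22 down to 11 per arm in range after 15% loss. The figure of about 27 holds only for an even age spread and should not be read as a forecast. The count of about 8 children crossing age 9 by month 11 rests on the same assumption.

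The consequence is a resilience result, and an ERE burden figure, that are hard to interpret if pooled over age. Acceptability and feasibility overall, the other secondary outcomes and the sample size are not undermined. The point should be settled before analysis, as a matter for one secondary outcome.

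**What to change.** Define the ERE outcome analysis on children aged 9 to 12 at baseline, and state its expected n alongside the full sample. Fixing eligibility by baseline age keeps the analysis set constant over all five assessments and deals with children who cross age 9.

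Where the ERE is given to children under 9, report their scores, blank items and completion time separately and do not pool them with the older group. This keeps the pilot's information on whether the form works in younger children, and it uses any baseline forms already collected, since recruitment has been open since 15 September 2015 (Trial status).

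An instrument suited to ages 6 to 8, or a stated justification for using the ERE below 9, would also answer the point, but each needs evidence that the article does not contain.

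The cost is wording plus a smaller n for this one outcome. Before loss, the in-range group would be about 25.5 down to 13 per arm over the assumed range. That is below the minimum of 30 per arm that the article cites for estimating parameters in feasibility studies, so ERE estimates taken into the full trial should be labelled as correspondingly imprecise.
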